## Abstract

**Background:**

Zika virus **(**ZIKV) has been identified in several body fluids of infected individuals. In most cases, it remained detected in blood from few days to 1 week after the onset of symptoms, and can persist longer in urine and in semen. ZIKV infection can have dramatic consequences such as microcephaly and Guillain-Barré syndrome. ZIKV sexual transmission has been documented. A better understanding of ZIKV presence and persistence across biologic compartments is needed to devise rational measures to prevent its transmission.

**Methods:**

This observational cohort study will recruit non-pregnant participants aged 18 years and above with confirmed ZIKV infection [positive reverse transcriptase-polymerase chain reaction (RT-PCR) test in blood and/or urine]: symptomatic men and women in ZIKV infection acute phase, and their symptomatic or asymptomatic household/sexual infected contacts. Specimens of blood, urine, semen, vaginal secretion/menstrual blood, rectal swab, oral fluids, tears, sweat, urine and breast milk (if applicable) will be collected at pre-established intervals and tested for ZIKV RNA presence by RT-PCR, other co-infection (dengue, Chikungunya, HIV, hepatitis B and C, syphilis), antibody response (including immunoglobulins M and G), plaque reduction neutralization test (if simultaneously positive for ZIKV and dengue), and ZIKV culture and RNA sequencing. Data on socio-demographic characteristics and comorbidities will be collected in parallel. Participants will be followed up for 12 months.

**Discussion:**

This prolonged longitudinal follow-up of ZIKV infected persons with regular biologic testing and data collection will offer a unique opportunity to investigate the presence and persistence of ZIKV in various biologic compartments, their clinical and immunological correlates as well as the possibility of ZIKV reactivation/reinfection over time. This valuable information will substantially contribute to the body of knowledge on ZIKV infection and serve as a base for the development of more effective recommendation on the prevention of ZIKV transmission.

**Trial registration:**

NCT03106714. Registration Date: April, 7, 2017

**Electronic supplementary material:**

The online version of this article (10.1186/s12879-018-2965-4) contains supplementary material, which is available to authorized users.

## Background

### Epidemiology

ZIKV is a mosquito-borne arbovirus in the family *Flaviviridae*, genus *Flavivirus* whose first isolation occurred in 1947 from a rhesus monkey in the Zika forest of Uganda [1]. The genus includes more than 70 viruses comprising important pathogens such as dengue, yellow fever, Japanese encephalitis and West Nile virus [2]. All flaviviruses include in their cycle a vertebrate host and insect vectors and many flaviviruses are clinically important as they elicit central nervous system diseases in infected individuals [3]. The primary mode of ZIKV transmission is through mosquito bites. The virus is almost exclusively transmitted by the *Aedes aegypti* mosquito but has been isolated from several other species of the genus Aedes such as *Aedes albopictus*, *Aedes africanus* and *Aedes luteocephalus* [4]. Any country where competent vectors are present bears risk for ZIKV outbreaks. In addition to the ongoing outbreak started in 2015 in South America, ZIKV has previously caused outbreaks in the Yap Islands, French Polynesia, New Caledonia, Cook Island and Easter Island [5]. The mosquito has a predilection for indoor environments which might explain its distribution reflecting patterns of human migration and urbanization [6]. Between 01/01/2007 and 02/06/2016 Zika was documented in 60 countries and territories of which 46 were experiencing their first outbreak since 2015 [7].

### Clinical manifestations of ZIKV infection

The most common symptoms of ZIKV infection are rash, fever, arthralgia, myalgia and conjunctivitis [8]. Recently a study in Rio de Janeiro, Brazil, identified maculopapular rash (97%) and pruritus (79%) as the two most common symptoms among confirmed cases [9]. Most of the patients with ZIKV infection have mild disease, but severe neurologic complications have been described in patients in French Polynesia and during the current outbreak in Brazil [10, 11].

ZIKV infection has become a major public health concern due to suspected causal relationship between ZIKV and microcephaly, amongst other neurological manifestations. The Pan American Health Organization/World Health Organization (PAHO/WHO) issued an alert in November 2015 in response to a large increase in the number of cases of microcephaly notified by the Brazil International Health Regulations National Focal Point. The country, which had its first autochthonous case confirmed in May 2015, and by November 2015 had spread to 15 states, experienced a staggering increase in rates of microcephaly in live births from 5.7/100,000 in 2010 to 99.7/100,000 by November 2015 [12]. This led the World Health Organization to declare the current outbreak as a Public Health Emergency of International Concern on 1 February 2016 [13].

Microcephaly is a rare neurological condition where babies are born with a small head in comparison to other babies of the same sex and age. The symptoms accompanying microcephaly depend on the level of disease severity and vary from mild to life threatening. There is no specific treatment for this condition. In addition to genetic factors, microcephaly can also be associated with other so-called STORCH infections, (i.e. syphilis, toxoplasmosis, rubella, cytomegalovirus and herpes simplex virus), maternal exposure to toxic substances and malnutrition during pregnancy [14].

### Asymptomatic ZIKV infection

Around 80% of individuals infected with ZIKV remain asymptomatic [4]. A likely man-to-woman sexual transmission of ZIKV between two asymptomatic persons was first reported in June 2016 [20]. Until this date all reported sexual transmissions implicated a male index case with symptoms of ZIKV infection. This finding may play a more important role than expected in the dynamic of ZIKV transmission. This is of concern mainly for pregnant women or those considering pregnancy and needs to be further investigated to inform counselling and recommendations.

#### Menstrual blood, vaginal and rectal secretions

Menstrual blood, vaginal and rectal secretions are associated with sexual activities and for this reason will be collected from participants in this study. This will contribute to improve knowledge on the presence of the ZIKV in these fluids so interventions and management practices can be devised. By the time this protocol was produced no report has been published on the detection of the virus in these body fluids.

### Sweat and tears

Studies on the detection of the ZIKV in sweat and tears have not been published up to June 2016. This is an opportunity to increase generalizable knowledge and reduce uncertainty about ZIKV infection and, according to the results, to contribute to public health recommendations and actions.

### Urine

The isolation of ZIKV in cell culture from urine was first described in 2014 in Canada [31]. The study reported the case of a Canadian traveler returning from Thailand who was initially diagnosed with dengue fever as result of preliminary laboratory investigations. Atypical dengue serological results, however, led the investigators to a reconsideration of infection by another flavivirus.

In February 2016 ZIKV was also isolated in Brazil where urine and saliva samples from 9 patients in Zika acute phase symptoms were inoculated in Vero cell culture resulting in one isolate returned from urine (and one from saliva) [32].

It was suggested that renal excretion of ZIKV can start around 4 days after symptom onset [33]. ZIKV RNA, however, has been found in urine 20 days after it was no longer detected in serum [34]. The urine has shown to yield positive results through PCR, in a patient with Guillain-Barré Syndrome after 21 days of the neurological symptoms onset [35].

### Gingival crevicular fluid

Gingival crevicular fluid (GCF), a serum transudate or inflammatory exudate present in the gingival crevice surrounding teeth, and saliva are identified as distinct body fluids. The constituents of GCF originate from serum, gingival tissues, and from both bacterial and host response cells. Whole saliva and GCF can be distinguished by the fact that the IgG content of the GCF is several times greater than that of saliva.

As this is a non-invasive means of diagnosis, monitoring of viral markers and assessing the host response in infectious disease, and because saliva collection is less technique-sensitive than GCF, collection the latter will also be performed in the participants. No reports on the presence of ZIKV in GCF have been published so far.

### Study hypothesis and objectives

Study Hypothesis*:* ZIKV can be shed in human body fluids long after the time of the acute infection. Persistence of ZIKV in different body fluids may vary due to the influence of circulating specific ZIKV IgM and IgG, as well as host and environmental factors.

#### Primary objectives

To assess the presence and duration of ZIKV and related markers (ZIKV specific RNA, antigen, antibodies, T cell response and innate immunity) in blood, semen, saliva, crevicular fluid, urine, vaginal secretions, menstrual blood, rectal swab, tears, sweat and breast milk of infected individuals who present to clinics during acute illness and convalescence and in their infected symptomatic and asymptomatic household/sexual contacts.To relate these parameters to host immunity over time and across different body fluids, to socio-demography factors as well as other host and environmental factors.

#### Secondary objectives

To analyse the presence and duration of ZIKV in bodily fluids amongst male and female adults aged 18 years and above over a 12 months period.To analyse the persistence of other markers (ZIKV RNA, IgM, IgG, antigen) of ZIKV infection in bodily fluids amongst male and female adults aged 18 years and above over a 12 months period.To explore potential relation between host and environmental factors as well as co-infections - dengue, chikungunya, HIV, syphilis, HBV, HCV, Oropouche virus (Bunyavirus), Mayaro virus and Yellow Fever (check immunization status) - on the duration of the persistence of the virus in body fluids. HIV, syphilis, HBV and HCV tests will be provided by the National AIDS control programme. The algorithms used by the programme for testing and treatment will be used.To assess the proportion of asymptomatic infections among household/sexual contacts to infected cases.To assess the possibility of reinfection or reactivation of the ZIKV cases over the study period.To describe concordance between RT-PCR test results, neutralizing antibodies, virus isolation, antigen results, and specific ZIKV antibody responses in these fluids.

## Methods/design

### Study design

This is a prospective observational cohort study. After signing a screening consent, male and female potential study participants presenting rash compatible with ZIKV infection in collaborating clinics will be tested for the presence of ZIKV in blood and urine. The following day, after providing informed consent for enrolment, those found to be RT-PCR positive for ZIKV infection, fulfilling all inclusion criteria will be enrolled and subject of regular collection of body fluids over a period of 12 months according to a pre-established schedule. Household/sexual contacts will be screened at the reference centers where the index case was diagnosed or if preferable at their household, and recruited following the same criteria. The standard care will be provided to all participants.

### Index case – Screening

**Screening inclusion criteria**
○ Being a man or woman aged 18 years and above○ Presenting rash compatible with ZIKV infection○ Having given consent to provide blood and urine for RT-PCR testing and to be enrolled if the tests return positive, including coming back to all follow-up visits and provide body fluid according to the testing schedule.○ Permanence for 12 months at a place that allows sample collection for this period

**Screening exclusion criteria**
○ Being under 18 years of age○ For women, being pregnant○ Presenting a condition that would not allow reliable informed consent (e.g. alcohol abuse and substance misuse)○ Lacking mental capacity to give informed consent to participation

### Index case - enrolment

**Enrolment inclusion criteria**
○ Presenting RT-PCR test positive for ZIKV in blood and/or urine specimens collected during screening○ Having given consent to provide all body fluid collection, as appropriate, according to the testing schedule

**Enrolment exclusion criteria**
○ Presenting RT-PCR test negative for ZIKV in blood and/or urine specimens collected during screening

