### Household contacts (or sexual contacts if index case lives alone) - enrolment

**Enrolment inclusion criteria-** As per index case**Enrolment exclusion criteria**
***-*** As per index case

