#### B. Participant enrolment

Cases will be enrolled at places where study nurses will be based: Fiocruz ambulatory, FMT-DVD ambulatory or MHC. As described earlier, MHC will only recruit participants screened within its structure, while Fiocruz ambulatory will recruit participants screened within its structure and also receive referral from the primary health centers and 24-h emergency units. The contact details of the participant will be collected and their eligibility assessed by the study nurse that is, whether they meet the inclusion criteria and doesn’t meet any of the exclusion criteria. After the eligibility checks, the study will be explained in detail to the participants, including what the collection of each body fluid will entail and the frequency at which body fluid specimens will be collected. After making sure the participants have no further questions about the procedures, they will be asked to sign an enrolment informed consent. Illiterate participants will have the consent form read to them in the presence of a witness, who will sign to verify the accurate reading of the form and agreement of the participant.

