### Sampling and sample size calculation

ZIKV is an emerging pathogen about which little information is known. This is a prospective observational cohort study, whose prediction of the exact sample size required cannot be prospectively determined. However, considering the scarcity of existing information on viral shedding, even a few participants would contribute to the body of evidence on the topic and lead to improved public health recommendations.

A multistage cluster sampling will be used to identify potential participants for inclusion and follow-up in the persistence cohort. All consecutive individuals RT-PCR positive for ZIKV in urine and/or blood identified during the screening process will be included in the cohort. In addition, all adult household/sexual contacts (symptomatic or asymptomatic) of these clinical cases, will be offered participation, and to be tested and included in the cohort if found RT-PCR positive for ZIKV in blood and/or urine.

The following is the rationale for estimating the sample size needed for body fluids other than blood, when we hypothetically estimate the prevalence of persistence will be 50% after 12 months. The below sample size calculations refer to estimating a population proportion at a certain point (or period) in time.

Using a population size (N) of 1,000,000 for finite population correction factor, and hypothesized rate of ZIKV persistence in at least one body fluid that is near 50% by the end of 12 months post-ZIKV infection, with a two-sided 95% confidence interval width of 10% (or margin of error (ME) of ±5%), a sample size of 385 males and 385 females who are either positive for ZIKV in urine or in blood at baseline will be needed.

The potential introduced design effect of the different clinic facilities used in the consecutive recruitment of study participants, will be explored both in stratified analyses by clinic, and in addition clinic will also be run as an independent variable in multivariate models.

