b)**Enrolment visit (Visit 1):** Laboratory results delivery - the day results for blood and urine specimens are available. The test result will be delivered to the participant by the study nurse at the enrollment site.
Negative RT-PCR for ZIKV in blood and urine

For individuals whose ZIKV RT-PCR tests performed on urine and blood returned negative, management will be done according to regular procedures and they will be referred back to the initial clinic where they were seen in the first place.Positive RT-PCR for ZIKV in blood or urine

Individuals whose RT-PCR tests performed on blood or urine are positive will be considered as index cases. The next steps will be the following:○ The nurse will explain in details what the full enrolment in the study entails and ask for an informed consent for the index case to continue in the full study.○ A detailed questionnaire will be applied (Enrolment questionnaire).○ The nurse will proceed with the specimen collection of all body fluids discussed previously with the index case, including new blood and urine specimens.○ The specimen collection schedule will proceed according to the time frame and intervals shown in Table 1.○ Specimens collected will be noted on forms.○ The nurse will also discuss with the index case the invitation of the household contacts/sexual partners to the study.

**Table 1 Tab1:** Time frame for collection of specimens

Time	Recruitment visit index case	Recruitment visit household member	Sample collection		
Visit 0	Sample collection	–	Blood and urine		
Visit 1 – inclusion visit	Visit 0 + 2 days				
	RT-PCR Results				
	-RT-PCR positive: individuals start follow up	Invitation to attend the clinic or household visit by the nurse (Blood and urine)			
	-RT-PCR negative: individuals are not included in the study				O
Visit 2	Visit 1 + 2 days	Visit 1 + 3 days			T
Visit 3	Visit 1 + 4 days	Visit 1 + 5 days			H
Visit 4	Visit 1 + 10 days	Visit 1 + 11 days	B		E
Visit 5	Visit 1 + 20 days	Visit 1 + 21 days	L		R
Visit 6	Visit 1 + 30 days	Visit 1 + 30 days	O	+	
Visit 7	Visit 1 + 60 days	Visit 1 + 60 days	O		F
Visit 8	Visit 1 + 90 days	Visit 1 + 90 days	D		L
Visit 9	Visit 1 + 120 days	Visit 1 + 120 days			U
Visit 10	Visit 1 + 150 days	Visit 1 + 150 days			I
Visit 11	Visit 1 + 180 days	Visit 1 + 180 days			D
Visit 12	Visit 1 + 210 days	Visit 1 + 210 days			S
Visit 13	Visit 1 + 240 days	Visit 1 + 240 days			
Visit 14	Visit 1 + 270 days	Visit 1 + 270 days			
Visit 15	Visit 1 + 300 days	Visit 1 + 300 days			

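### Internal inconsistency: the enrolment exclusion, read literally, bars people RT-PCR positive in only one of blood and urine, whom the inclusion criterion and the rest of the protocol enrol

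*Protocol article*

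**What the plan says.** Under the index case enrolment heading, the inclusion criterion is "Presenting RT-PCR test positive for ZIKV in blood and/or urine specimens collected during screening" and the exclusion criterion is "Presenting RT-PCR test negative for ZIKV in blood and/or urine specimens collected during screening". The two sentences differ only in the words positive and negative. For household contacts (or sexual contacts), both enrolment lists say "As per index case".

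The Participant enrolment section tells the study nurse how to combine the lists. Eligibility means checking "whether they meet the inclusion criteria and doesn’t meet any of the exclusion criteria".

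The Admission procedure, under Enrolment visit (Visit 1), uses a different rule. The people referred back are described this way: "For individuals whose ZIKV RT-PCR tests performed on urine and blood returned negative, management will be done according to regular procedures". For the others it states: "Individuals whose RT-PCR tests performed on blood or urine are positive will be considered as index cases". The Sampling and sample size calculation section agrees with Visit 1: "All consecutive individuals RT-PCR positive for ZIKV in urine and/or blood identified during the screening process will be included in the cohort".

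**The concern.** The negation of being positive in at least one fluid is being negative in both. The exclusion criterion instead keeps the and/or of the inclusion criterion, so it covers a negative result in either fluid. Anyone with discordant results is then included by one line and excluded by the next.

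Two things are at stake. The first is conduct. The protocol names three cities (Rio de Janeiro, Manaus and Recife) and several kinds of referring clinic. Referring staff are to be briefed on the eligibility criteria in particular, and nurses judge eligibility against the lists. One site could follow the list and another the Visit 1 procedure. If all follow Visit 1, every discordant participant enrolled formally meets a written exclusion criterion, in a study whose monitoring committee reviews protocol compliance.

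The second is the population. If the list were applied literally, the cohort would contain only people positive in both fluids. That selects on detectability at baseline, which may be related to the persistence outcome, and it would also reduce the number who can be recruited towards 650 males and 650 females.

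**Working it through.** The protocol gives no figure to reproduce on this point. The check is one of logic.

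**Inputs**
- Inclusion: positive in blood, or urine, or both (index case, Enrolment inclusion criteria).
- Exclusion as written: negative in blood, or urine, or both (index case, Enrolment exclusion criteria).
- Combination rule: inclusion met and no exclusion met (Participant enrolment).

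**All four result combinations**

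| Blood | Urine | Inclusion met | Exclusion met, as written | Eligible as written | Eligible if exclusion means negative in both |
|---|---|---|---|---|---|
| + | + | yes | no | yes | yes |
| + | − | yes | yes | **no** | yes |
| − | + | yes | yes | **no** | yes |
| − | − | no | yes | no | no |

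As written, both discordant rows meet the inclusion and the exclusion at once, and only the double-positive row is eligible. With the exclusion read as negative in both, the eligible rows are exactly those that meet the inclusion criterion.

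**Which rule the other sections use**
- Enrolment visit (Visit 1): sent back if negative in urine and blood; index case if positive in blood or urine.
- Household/sexual contacts, under recruitment: asked for enrolment consent if either fluid is positive.
- Household/sexual member, Enrolment visit: proceeds if blood or urine is positive.
- Sampling and sample size calculation: includes everyone positive in either fluid, and the 385 per sex before inflation is defined on people positive in urine or in blood at baseline.
- Follow-up procedures: follows those positive in either fluid.
- Data analysis plan: bases the analysis primarily on those positive in blood or urine at baseline.

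All six agree with the last column of the table and conflict with the column before it.

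**Whether discordant results are to be expected.** The Background gives reasons to expect them in both directions. The Urine section says renal excretion may start around 4 days after symptom onset, which allows blood-positive, urine-negative results early. It also reports RNA in urine 20 days after serum had become negative, which allows the reverse later. The Saliva section describes one case with RNA in urine up to day 29 and in plasma up to day 10. None of this gives a frequency of discordance at screening.

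**The case against.** The strongest reply is that nobody could mistake the intent. The either-fluid rule is stated repeatedly, including in the step-by-step procedure that the nurse follows at Visit 1. The exclusion looks like the inclusion sentence with one word changed and the and/or left behind. The sample size and the analysis population already use the either-fluid rule and do not depend on the exclusion line. Nothing in the protocol suggests that any site would turn discordant people away.

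Most of this stands. It is a drafting slip and not a chosen design, and it would be wrong to say that the cohort will consist of double-positives. It does not remove the need for correction: an eligibility list is an operative text, and this one bars part of the stated analysis population.

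A reader might infer more, and three such inferences are not supported:

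- That blood-negative, urine-positive is the commonest discordant pattern. The report of urine RNA 20 days after serum clearance concerns late persistence, whereas index cases are tested when they present with rash in the acute phase. No frequencies are given.
- That double-positives are early presenters with higher viral load, so that the bias has a known direction. No section says so. If urinary excretion starts around day 4, the earliest presenters could be positive in blood only.
- That the share lost can be stated. With assumed positivity b in blood and u in urine, and independence, the discordant share of any-positive people is 1 − bu / [1 − (1 − b)(1 − u)]. This gives 1 − 0.81/0.99 = 18% at 90% each, and 1 − 0.25/0.75 = 67% at 50% each. These values are purely hypothetical. The positivity rates are not in the protocol, and results from the same person are unlikely to be independent; positive correlation would lower the share at the same positivity.

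**Conclusion.** The point holds as an internal inconsistency in the eligibility criteria, wrong as written. Taken literally with the rule that no exclusion may be met, the criterion makes people positive in one fluid only ineligible, both index cases and contacts. The inclusion criterion admits them, and the recruitment, sampling, Visit 1, follow-up and analysis sections enrol, follow and analyse them.

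In terms of patterns, two of the three any-positive combinations are affected. In terms of people, the size cannot be computed from the protocol. The practical effect depends on which text each site follows: none on who enters if all follow Visit 1 (though formal deviations would remain), and restriction to double-positives wherever the list is followed. In the latter case the selection may bear on persistence, in a direction that the documents do not establish. The logical conclusion rests on reading and/or in its ordinary inclusive sense and needs no numerical assumption.

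**What to change.** Reword the index case enrolment exclusion so that it applies only when both screening specimens, blood and urine, are RT-PCR negative for ZIKV. The contacts' criteria then follow through their existing cross-reference. Send the corrected wording to the three sites and their referring clinics, and ask each site which rule it has been applying, so that anyone turned away or recorded as a deviation on this ground can be identified.

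The cost is a one-line amendment and a site memo. The sample size, tests, visits and analysis population stay as they are, because they already assume the either-fluid rule.
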